### Outcome measures

The primary and secondary outcomes measures will be assessed by a physical therapist specialised in pelvic floor rehabilitation and the physician-investigator. The sample will be characterised based on sociodemographic [age, body mass index (BMI), duration of symptoms, number of pregnancies, number of vaginal deliveries, ethnicity and educational level)] and clinical (urinary symptoms, PFM function, quality of life) variables.

#### Primary outcome measure

The primary outcome measure will be the objective cure of UI as assessed by means of the 1-h pad test 6 months after randomisation. For the 1-h pad test, the women will be asked to wear pre-weighed pads and drink 500 ml of sodium-free liquid in < 15 min. After rest, they will be instructed to exercise for 30 min, including walking, climbing up and down five flights of stairs (10×), jumping (10×), coughing vigorously (10×), bending to pick up an object from the floor (10×) and washing hands for 1 min in running water. Before and after the test, the weight of the pad will be measured with a high-precision balance to determine the amount of leakage. For the 1-h pad test, an increase of 1 to 10 g represents mild incontinence and 11 to 50 g represents moderate incontinence. Women with urine leakage ≥ 2 g will be included because the study will be conducted in a tropical country [17]. The objective cure of urine loss after the intervention will be defined as leakage < 2 g. The pad test is considered a relevant tool for the assessment of UI treatment success and has been widely used in this type of study [30–32].

#### Secondary outcome measures

The secondary outcomes will be assessed according to the recommendations formulated by the International Continence Society [33]. The instruments with the best psychometric properties (validity, reliability and responsiveness to change) were selected for each outcome.
*The 3-day bladder diary:* This validated instrument assesses daytime/night-time urine leakage episodes during three consecutive days [18].*The 1-h pad test:* This test assesses urine leakage in situations involving effort. For the 1-h pad test, an increase of 1 to 10 g represents mild incontinence and 11 to 50 g represents moderate incontinence [17]. The results will be rated positive when the variation in the pad weight is ≥ 2 g because the study will be conducted in a tropical country.*The International Consultation on Incontinence Questionnaire – Short Form (ICIQ-SF):* A four-item questionnaire that evaluates the impact of symptoms of incontinence on quality of life and outcome of treatment (0–21 overall score, with greater values indicating increased severity) [19].*The Incontinence Quality of Life Questionnaire (I-QoL):* The impact of SUI on quality of life will be assessed by the Incontinence Quality-of-Life Questionnaire (I-QoL). The I-QoL evaluates the limitations on human behaviour, psychosocial impact and social embarrassment [20].*Subjective cure of SUI:* The subjective cure will be measured by asking the patients if they were “satisfied” or “dissatisfied” about their condition (urinary incontinence) after treatment. We considered them to be “satisfied” when the patient was happy with the results and did not want a different treatment and “dissatisfied” if the patient desired a treatment other than the initial one [18].*Frequency of the outpatient sessions:* The frequency of the outpatient sessions will be monitored by the physiotherapist and will be expressed as a percentage of the total sessions anticipated for 3 months of supervised treatment. The participants will visit the outpatient clinic twice per month to perform training under supervision by a physical therapist. By the end of the 3-month treatment period (excluding the baseline and final assessments), the participants will have performed six intervention sessions.*Adherence to home exercises:* The number of completed exercise sets will be obtained using an exercise diary, and it will be recorded as the mean of the exercise sets per month performed during the 3-month therapy intervention for both groups. The number of home exercise sets in both groups will also be assessed at the 6-month follow-up [34]. The participants must register how many times in the day they performed the indicated series of exercises (once, twice or three times per day) and the day they were performed (to calculate how many days in the month the exercises were actually performed). At the end of each month, the participants are expected to have performed the exercises for at least 12 days (3 days per week) (36 days by the end of the 3-month supervised period and 6-month follow-up). The participants will be directed to make records only when the exercises were effectively performed. The participants are expected to perform at least nine series of exercises per week for a total of 36 per month. At the end of the 3-month period of supervised training, following the primary and secondary assessments, the participants will be directed to continue the training at home (according to the protocol corresponding to the group of allocation) and will be given three diaries of exercise frequency (with the due dates) to record the exercises performed throughout the 3 months of unsupervised training at home.Self-efficacy/outcome expectation to PFM exercises: The scale contains 17 questions in the format of a visual analogue scale with answers ranging from 0 (not confident at all) to 100 (the most confident). Thirteen items refer to self-efficacy and four to outcome expectations. The final scores will be obtained by calculating the mean of the items, ranging from 0 to 100, in which higher values are equivalent to more beneficial self-efficacy/outcome expectation to PFM exercises [21].PFM function, strength and vaginal squeeze pressure: The aim of physical and functional pelvic floor assessment is to investigate the muscle integrity and contractile ability of the pelvic muscles [35]. All the procedures will be performed with the participants in the lithotomy position.
*Function of the PFM (digital palpation):* PFM function will be assessed through two-finger vaginal palpation. The examiners will place the fingers at about 4 cm of the vaginal introitus, and the muscle function will be assessed by means of the PERFECT scheme. PFM strength will be assessed by the modified Oxford Grading Scale (scores of 0–5) [22]. The volunteers will be instructed to perform three contractions lasting 5 s with the greatest strength possible (maximum PFM contractions); these periods of contraction were interrupted by 1-min rest periods. Endurance will be expressed as the length of time for up to 10 s that a maximal vaginal contraction could be sustained. Thus, the contraction will be timed until the muscle started to fatigue. The number of fast maximal PFM contractions that could be repeated (up to 10) will be reported as the fast contraction variable [23].*PFM strength:* An intravaginal dynamometric speculum (Miotec®) (Porto Alegre, Rio Grande do Sul, Brasil), *New Miotool Wireless*, will be used. The vaginal dynamometer will measure resistance to unidirectional and anteroposterior compression in kilogrammes/force (kgf). The participants will be requested to perform three maximum voluntary contractions (MVCs) of the PFMs at 3-min intervals. The best of three consecutive attempts was registered as the MVC [36].*Vaginal squeeze pressure:* A vaginal balloon catheter connected to a pressure transducer (Peritron manometer-Cardio DesignTM, Victoria, Australia) will be used to assess the vaginal squeeze pressure [24]. The best of three consecutive attempts will be registered as the MVC [36].

### Trial management

The principal investigator (PI) ([name]) and a research coordinator ([name]) will regularly communicate (through emails, telephone or in person) to promote and monitor the recruitment progress. The PI, the evaluators and physiotherapists will conduct conference calls or face-to-face meetings to monitor the study’s progress. All members of the research team will be informed of the progress through e-mail every 2 weeks. All the data collected will be anonymised and stored in a locked cabinet in (blinded). After each assessment and on the same day, the files will be reviewed by the research assistant to identify missing data. Any missing information will be retrieved immediately by research assistants directly from the study participants. The data will be entered weekly (depending on recruitment rate) into a computerised database, SPSS [Statistical Package for Social Sciences (SPSS Inc., Chicago, IL, EUA)], version 22.0. A final quality-control step will be performed at the time of the data analysis by the trial statistician. Frequency distributions and ranges will be analysed to detect any outliers that could signal potential errors. The data will be analysed without any nominative identifiers.

### Adverse events

In the current study, there are no anticipated risks or inconveniences, as the applied interventions and examinations are well established and widely applied in standard pelvic floor physiotherapy. All of the women will be asked during every physiotherapy and measurement consultation whether they are experiencing any adverse effects. If there are any complications or any complications are suspected, the patients will be instructed to contact a member of the study team, and they will be informed of the procedure to follow for other episodes. The Trial Steering Committee (TSC) is made up of three researchers ([name], [name] and [name]); they will meet weekly and analyse the ongoing results of the research. They will have the power to partially or completely halt the course of the study. No public organisations were involved in the development of this study.

### Sample size calculation

The literature on the Knack is scarce and assessed only in combination with PFMT [16, 26]. The aim of this study is to investigate the effects of the Knack alone for the treatment of SUI. Because of the lack of scientific evidence a local pilot study was previously conducted to calculate the sample size (unpublished). Forty-five patients agreeing to participate by signing an informed consent form (Additional file 1) will be recruited. This group will be randomly allocated by means of online randomisation software (http://randomization.com) to the following groups: the Knack, PFMT or PFMT + the Knack. The primary outcome measure [objective cure as established by means of the 1-h pad test (leakage ≤ 2 g)] will be used to compare the effects of SUI treatment amongst the groups. At the end of the pilot study (after the last randomised patient completes the intervention), the percentage of cured participants will be compared amongst the groups. Based on a pilot study, it is observed that the PFMT group has a higher objective cure rate compared to the knack group, however, without statistical significance at the level of 5% (*p* value = 0.592 obtained through Fisher’s exact test). Although the knack group has an objective cure rate lower than that of the PFMT group, this objective cure rate is approximately equal to 50%. The premises for the sample calculation are the hypotheses: *H*_0_: θ_1_ − θ_2_ ≤ δ and *H*_*a*_: θ_1_ − θ_2_ > δ, where, θ_1_: response rate of the Knack group; θ_2_: response rate of the PFMT group (gold standard); *δ*: Non-inferiority margin (clinically relevant difference between the response rates of groups the Knack and PFMT, and that for the calculation of non-inferiority, the value of *δ* must be negative; *r*: ratio between sample sizes *n*_2_/*n*_1_ (*r* = 1 ⇒ *n*_2_ = *n*_1_); *α*: significance level (*α* = 5%); 1 − *β*: test power (*β* = 20% ⇒ 1 − *β* = 80%) [37]. Formula:
$$ {\displaystyle \begin{array}{c}{n}_1=\frac{{\left({z}_{\alpha }+{z}_{\beta}\right)}^2\left[r{\theta}_1\left(1-{\theta}_1\right)+{\theta}_2\left(1-{\theta}_1\right)\right]}{{\left({\theta}_1-{\theta}_2-\delta \right)}^2}\\ {}{n}_2={rn}_1\end{array}} $$

Notice that, here, *r* = 1 for equal size *n*_1_ = *n*_2−_

Thus, according to the result of the pilot sample, at the 5% significance level, there is no significant difference between the groups in relation to the objective cure rate in the treatment of mild and moderate SUI, assessed by the 1-h pad test. Considering the premises: θ_1_= 42.9% and θ_2_= 71,4% (obtained through the analysis of the pilot sample), *δ* = − 7,14% (10% variation in relation to the response rate of the PFMT group, obtained through literature data [38], *r* = 1 (groups of equal sample sizes), *α* = 5% and *β* = 20% ⇒ power (1 – *β*) = 80%, we obtained a total of 122 patients (61 patients per group). Thus, considering a significance level of 5%, a sample of 122 patients (61 patients per group) has 80% power to show the non-inferiority of the knack technique compared to PFMT in the treatment of mild and moderate SUI, with a non-inferiority margin of − 7.14%, which corresponds to a variation of 10% in relation to the response rate of the PFMT group (gold standard), supposedly equal to 71.4% and assuming that the rate of response of the test group is 42.9%. The sample size calculation was based on the primary objective of comparing the Knack technique (experimental group) with PFMT (control group). However, we have a third group that associates the techniques PFMT + the knack, so, 183 participants will be recruited. It is also necessary to consider possible losses in the sample during the 6-month follow-up period, thus, we assume losses of 0 to 15% based on previously published studies [39, 40]. Thus, we will recruit nine more participants per group, increasing the total number of participants to 210.

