### Aim and objectives

The aim of the study is to investigate the effects of voluntary PFM pre-contraction alone during activities involving an increase of the intra-abdominal pressure (the Knack) for the treatment of female SUI.

The objectives are to compare the effectiveness of the Knack alone versus PFMT alone and PFMT + the Knack for the following measures:
Objective cure of urine leakage after intervention, defined as leakage of < 2 g (on the 1-h pad test) immediately after the intervention and 6 months after randomisation (primary outcome measure) [17].Lower urinary tract symptoms and impact of UI on the participants’ quality of life immediately after the intervention and 6 months after randomisation. These secondary outcomes will be assessed by means of the 3-day bladder diary, which considers the number of episodes of urine leakage on efforts [18]; the 1-h pad test, which evaluates the severity of urine leakage [17]; the International Consultation on Incontinence Questionnaire – Short Form (ICIQ-SF), which investigates urinary symptoms [19]; and the Incontinence Quality of Life Questionnaire (I-QoL), which is a measure of quality of life [20].Self-perceived efficacy of exercises immediately after intervention and 6 months after randomisation. This parameter will be assessed by means of the Self-Efficacy Scale for Practising Pelvic Floor Exercises [21]; satisfaction and desire to perform some other treatment immediately after the intervention and 6 months after randomisation (participants will be rated “satisfied” when they do not manifest a wish to perform some other treatment and as “dissatisfied” when they do wish to perform some other treatment) [18].PFM strength function as measured by digital palpation (PERFECT scheme) [22, 23], Peritron manometer [24] and pelvic floor dynamometry immediately after the intervention and 6 months after randomisation.

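### The sample-size section uses a different cure cut-off from the rest of the protocol, and its planning rates and flat 80% power rest on 14 pilot women

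*Protocol article*

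**What the plan says.** **Cure rule.** The primary outcome section says "The objective cure of urine loss after the intervention will be defined as leakage < 2 g", and the objectives use the same strict inequality. The sample-size section describes the same primary outcome as "objective cure as established by means of the 1-h pad test (leakage ≤ 2 g"). On entry, the primary outcome section says "Women with urine leakage ≥ 2 g will be included".

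**Pilot.** The sample-size section introduces it with "Forty-five patients agreeing to participate by signing an informed consent form", to be randomised to three groups. Cure is to be compared at the end of the pilot, "after the last randomised patient completes the intervention". The reported result is Fisher's exact p = 0.592 for PFMT against the Knack. No denominators are given.

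**Use of the pilot.** Cure rates of 42.9% (Knack) and 71.4% (PFMT) are attributed to the pilot. The margin is −7.14 points, which is 10% of 71.4%, and a literature source is cited for the 10%. From these the section derives 61 per group with 80% power at the 5% level.

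**Time of the primary outcome.** The primary outcome section has "objective cure of UI as assessed by means of the 1-h pad test 6 months after randomisation". The objectives have "immediately after the intervention and 6 months after randomisation (primary outcome measure").

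**The concern.** One primary outcome carries two cut-offs, and one of them overlaps the entry criterion. Under ≤ 2 g, a woman who enters at exactly 2 g and does not change counts as a success.

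The planning rates also look better founded than they are. A reader told of 45 patients in three groups would suppose about 15 per arm, but 42.9% and 71.4% cannot arise from 15 women. If the real denominators are much smaller, the rates, and the margin scaled from one of them, carry little information. A power statement without a range then gives false assurance about what 61 per group can show.

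**Working it through.** **1. Reproduce the stated sample size.** Inputs from the sample-size section: θ₁ = 0.429, θ₂ = 0.714, δ = −0.0714, 80% power, 5% level (taken as one-sided).

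- Standard variance: 0.429 × 0.571 + 0.714 × 0.286 = 0.4492.
- (1.645 + 0.842)² = 6.183.
- Denominator: (0.429 − 0.714 + 0.0714)² = (−0.2136)² = 0.04562.
- n = 6.183 × 0.4492 / 0.04562 = 60.9, so 61 per group. This matches.

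The formula as printed has θ₂(1 − θ₁) where the standard term is θ₂(1 − θ₂). With the printed term the same inputs give 88.4, so 89 per group. The stated 61 therefore came from the standard term.

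**2. Recover the pilot denominators.** Within 45 patients, the two rates to one decimal arise only when both arm sizes are multiples of 7. Two-sided Fisher p-values:

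| Knack | PFMT | p |
|---|---|---|
| 3/7 | 5/7 | 0.592 |
| 9/21 | 5/7 | 0.385 |
| 6/14 | 5/7 | 0.362 |
| 3/7 | 10/14 | 0.346 |
| 6/14 | 10/14 | 0.252 |

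Every other admissible pair gives a smaller p than 0.385. By hand for 3/7 against 5/7: there are 8 cures among 14 women, and C(14,7) = 3432 tables. The observed table has weight C(8,3) × C(6,4) = 840. Only the table with 4 Knack cures is more likely, at 70 × 20 = 1400. So p = (3432 − 1400)/3432 = 0.592.

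A three-group exact test reaches 0.592 only with arms of 7, 7 and 29, which again puts 7 women in each of these two arms.

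**3. Precision of the rates.**

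- Exact 95% intervals: 3/7 gives 9.9% to 81.6%; 5/7 gives 29.0% to 96.3%.
- Difference: 3/7 − 5/7 = −28.6 points.
- Newcombe interval, from Wilson limits 15.8–75.0% and 35.9–91.8%:
  - lower: −0.286 − √(0.270² + 0.204²) = −0.62
  - upper: −0.286 + √(0.321² + 0.355²) = +0.19

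**4. Power at 61 per group.** The alternative hypothesis in the section is θ₁ − θ₂ > δ, so power = Φ[(θ₁ − θ₂ − δ)/SE − 1.645], with SE = √{[θ₁(1 − θ₁) + θ₂(1 − θ₂)]/61}. PFMT is held at 71.4% and δ at −7.14 points.

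| Knack rate | SE | (θ₁ − θ₂ − δ)/SE | Power |
|---|---|---|---|
| 42.9% | 0.0858 | −2.49 | about 0.002% |
| 60% | 0.0853 | −0.50 | about 2% |
| 71.4% | 0.0818 | 0.87 | about 22% |
| 80% | 0.0773 | 2.04 | about 65% |

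The first row is near zero because the assumed difference of −28.5 points lies beyond the margin. Squaring the denominator in step 1 hides that sign.

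**5. Time point.** The pilot appears to have been read at the end of the intervention. That agrees with one of the two primary times in the objectives, but not with the single 6-month time in the primary outcome section.

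**The case against.** Several points on the other side stand.

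- The ≤ sign may be a one-character slip. It appears only in the pilot description, and the two rules differ only at exactly 2 g. No affected woman can be identified from the documents, so it is not established that the pilot was scored under a different rule.
- The 45 is written in the future tense and may be a planned number. The 7 per arm is inferred for the Knack and PFMT arms only; the third arm's size is unknown. A condensed article may leave pilot denominators to a fuller document. The figures it does print still fix them at 7 and 7.

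Four stronger readings are tempting, and the documents do not support them.

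- *The pilot time point is simply wrong for the trial.* The objectives list the end of the intervention as a primary time too. The text dates the end of the pilot and does not say when each woman's pad test was done. The firm finding is that the two statements of the primary time disagree.
- *Non-significance in the pilot is a premise of the design.* The section does say "there is no significant difference between the groups in relation to the objective cure rate", but its listed premises are the two rates, the margin, the ratio, alpha and power. The p-value is not among them, and the calculation assumes a wide gap.
- *The whole margin comes from 14 women.* The 10% fraction is attributed to literature. Only the 71.4% it multiplies comes from the pilot.
- *One woman moves the sponsor's sample size from 20 to 545.* Those figures, for 2/7 and 4/7 against 5/7, use the standard variance. The printed formula gives about 35 and 668. The fall when the Knack looks worse is an artefact of the squared denominator, so neither pair is a fair measure of the pilot's imprecision.

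**Conclusion.** The point holds in two parts. First, the cut-off in the sample-size section contradicts the trial's definition of cure and overlaps the entry rule. The effect on the cure rates cannot be computed from the documents, and it is confined to women at exactly 2 g. Second, the Knack and PFMT planning rates rest on 14 women, with intervals so wide that the difference could lie anywhere from about −62 to +19 points. The unqualified 80% power at 61 per group is not supported: across Knack rates from 42.9% to 80% it runs from near 0% to about 65%, and it is about 22% if the two treatments are equal.

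This assumes that the rates are printed correctly to one decimal, that p = 0.592 is a two-sided Fisher test of these two arms (or a three-group exact test, which leads to the same 7 and 7), that the 5% level is one-sided, and that the normal approximation holds with PFMT at 71.4%. The disagreement over the primary time is a separate inconsistency that needs reconciling.

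**What to change.** 1. Use < 2 g as the cure rule throughout, including the sample-size section.
2. Re-tabulate the existing pilot pad weights under that rule. Report the denominator in each arm, the time of the pad test, and the rates with confidence intervals, and explain how they relate to the 45 patients described. The text also calls the Knack rate roughly 50%, which should be squared with 42.9%.
3. Reconcile the objectives with the primary outcome section on whether the primary time is 6 months alone or also the end of the intervention.
4. Replace the single 80% statement with power over a range of cure rates, in the correct direction of the non-inferiority test and with θ₂(1 − θ₂) in the variance. The table in step 4 of the working can serve as a template.

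The cost is rewording and a re-tabulation of data already held, with no new patients. With 185 of 210 recruited at the time of the article, the cure rule can still be settled before the analysis, which is planned after the last final assessment. The downside is a less favourable stated power.

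### The stated 80% power for non-inferiority is false: the planning rates put the Knack 28.5 points below PFMT against a 7.14-point margin, so power is about 0.002%

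*Protocol article*

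**What the plan says.** All of this is in the Sample size calculation section of the protocol article.

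- **Hypotheses.** H0: θ1 − θ2 ≤ δ against Ha: θ1 − θ2 > δ, where θ1 is the cure rate with the Knack and θ2 the rate with PFMT. δ is described as the "Non-inferiority margin (clinically relevant difference between the response rates of groups the Knack and PFMT" and has to be negative.
- **Planning values.** The calculation is made "assuming that the rate of response of the test group is 42.9"%, with the PFMT rate "supposedly equal to 71.4"%. The margin is −7.14%, "which corresponds to a variation of 10% in relation to the response rate of the PFMT group (gold standard"). Alpha is 5%, power 80% and the allocation ratio 1.
- **Conclusion drawn.** With 61 women in each of the two arms, 122 in all, the design is said to be one that "has 80% power to show the non-inferiority of the knack technique compared to PFMT in the treatment of mild and moderate SUI". A third arm brings the number to 183, and nine more per group for losses bring it to 210.
- **Source of the rates.** A local pilot, for which the text gives "Forty-five patients agreeing to participate by signing an informed consent form", randomised to three arms. The Knack and PFMT cure rates were compared by Fisher's exact test, p = 0.592. No counts are given.

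**The concern.** A non-inferiority sample size must be computed at a true difference that lies inside the alternative, here above −7.14 points. The plan computes it at 42.9 − 71.4 = −28.5 points, where the Knack is inferior by about four times the margin. A valid non-inferiority test should almost never succeed there, so 80% power cannot be right.

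The section links the sample size to the primary comparison of the Knack with PFMT. If the claim stands, readers will take a result that misses the margin as coming from a trial with good power to meet it. In fact the trial had almost no chance under its own assumptions, and a poor one even if the two treatments were equal.

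**Working it through.** **Inputs (Sample size calculation section).** θ1 = 0.429, θ2 = 0.714, δ = −0.0714, 61 per group (70 after the allowance for losses). Alpha is taken as one-sided 5%, because the hypotheses are one-sided and the formula uses z_α; one-sided 2.5% would give 78 per group, not 61. So z_α = 1.645 and z_β = 0.842.

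**Step 1: reproduce the plan's number.**

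n = (z_α + z_β)² × [θ1(1 − θ1) + θ2(1 − θ2)] / (θ1 − θ2 − δ)²

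- Distance: 0.429 − 0.714 + 0.0714 = −0.2136
- Variance sum: 0.429 × 0.571 + 0.714 × 0.286 = 0.4492
- n = (1.645 + 0.842)² × 0.4492 / (−0.2136)² = 60.87, rounded up to 61

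The plan's 61 is recovered, but the distance is negative and squaring removes the sign. This uses the standard variance term θ2(1 − θ2). The formula as printed has θ2(1 − θ1), which gives 88.4, so 89 per group. That is probably a misprint.

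**Step 2: power in the direction of Ha.**

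SE = √(0.4492 / 61) = 0.0858

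Power = Φ((θ1 − θ2 − δ)/SE − z_α) = Φ(−0.2136/0.0858 − 1.645) = Φ(−2.49 − 1.645) = Φ(−4.13)

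| Setting (42.9% vs 71.4%, margin −7.14 points) | Power for non-inferiority |
|---|---|
| 61 per group, one-sided 5% | 0.0018% (exact binomial enumeration 0.0022%) |
| 70 per group, one-sided 5% | 0.0008% |
| 61 per group, one-sided 2.5% | 0.0004% |
| 61 per group, one-sided 5%, variance as printed | 0.010% |

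Power falls as n rises, so no larger sample can rescue the claim at these rates.

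**Step 3: what the 80% is.** With the sign reversed, Φ(+2.49 − 1.645) = 80.1%. That is the probability of showing that the Knack is worse than PFMT by more than 7.14 points.

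**Step 4: scale under kinder assumptions.** These scenarios are not in the plan.

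- Both true rates 71.4%: SE = √(2 × 0.714 × 0.286 / 61) = 0.0818, and power = Φ(0.0714/0.0818 − 1.645) = 22% (24% with 70 per group). Power of 80% needs 496 per group.
- For 80% power with 61 per group and PFMT at 71.4%, the true Knack rate would have to be about 83%, or 11.6 points better than PFMT.
- With equal true rates between 50% and 71%, the smallest margin with 80% power is about 20 to 23 points (61 per group) or 19 to 21 points (70 per group).

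**Step 5: what the size does support.** A two-sided 5% test of 71.4% versus 42.9% as a difference has about 90% power with 61 per group and 93% with 70. The 95% interval for the difference has a half-width of 1.96 × 0.0858 = 16.8 points at the pilot rates and 1.96 × 0.0818 = 16.0 points at equal rates of 71.4%, both with 61 per group.

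**Step 6: the pilot rates.** Forty-five women in three equal arms would be 15 per arm, and no count out of 15 gives 42.9% or 71.4%. Fisher's exact test gives p = 0.592 for 3/7 versus 5/7, the stated value, but p = 0.252 for 6/14 versus 10/14. A search over other denominators found no other match. The rates therefore appear to rest on 14 women, with exact 95% intervals of 10 to 82% (3/7) and 29 to 96% (5/7).

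**The case against.** Four points can be made for the plan.

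- **61 is correct arithmetic on the standard formula.** True. The error lies in the premise and direction: the planning point is inside H0. The printed formula does not give 61, but the misprint does not change the conclusion.
- **Non-inferiority is not advertised throughout.** It appears only in the sample size section. The abstract and objectives speak of comparing effectiveness, and the Statistical analysis section names ANOVA. This stands, and limits how widely the claim is spread. It does not make the claim true, and that section ties the size to the primary comparison.
- **The pilot denominators are inferred.** This also stands. No counts are given, the match assumes that the Fisher test compared only these two arms, and seven per arm could be a subset of the 45. The inference is strong, but it is a side point; the power result does not depend on it.
- **Equal rates of 71.4%, a Knack rate of 83% and the 50 to 71% range are the review's scenarios.** They are, and serve only to show scale. The main result uses the plan's own figures alone.

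Nothing elsewhere in the article rescues the 80%. The rates, margin and power are stated in prose, so this is not a damaged formula.

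**Conclusion.** The concern holds, with high confidence, and must be fixed. At the plan's own rates and margin, power for non-inferiority is about 0.002% with 61 per group, not 80%. The conclusion is the same at one-sided 5% or 2.5%, with 61 or 70 per group, by normal approximation or exact enumeration, and with either variance term. If the two treatments were equally effective at 71.4%, power would still be only 22 to 24%. The evidence behind the planning rates also looks thin, probably seven women per arm, although that part is inference.

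**What to change.** Keep the planned 210 and do not enlarge the trial to pursue this margin. The Trial status section reports 185 of 210 recruited, so the text can be corrected before the final analysis.

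1. Delete the 80% non-inferiority claim and replace it with, for example: *With 61 evaluable women per arm, power for non-inferiority at −7.14 points (one-sided 5%) is below 0.01% under the pilot rates and about 22% if both true rates are 71.4%.*
2. State what the size supports: about 90% power (two-sided 5%) to detect 71.4% versus 42.9% as a difference, and a 95% interval with a half-width of about 16 to 17 points.
3. Say in advance that the main result is the estimated difference in cure rates with its interval, and that failing to clear −7.14 points will be reported as non-inferiority not shown. The Statistical analysis section should name this comparison.
4. Give the pilot numerators and denominators behind 42.9% and 71.4%, and correct the variance term in the printed formula.

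The cost is a rewritten sample size section, a sentence in the analysis section and a registry note. No extra patients are needed. The price is a much less favourable power statement.
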